**FIGURE 2 pri70101-fig-0002:**
[figure not shown]
Research team and flow. T0: Initial assessment (baseline). T1: Assessment will be performed respecting a 7‐day interval after the baseline assessment. T2 and T3: Assessment will follow the same procedure as T1, with a 7‐day interval between each protocol (T1, T2 and T3), so that the patient will perform the other two training protocols. T4: assessment one week after the T3 assessment.

### Intervention and Comparator

2.6

The research will be conducted in a *blinded* manner after the publication of this protocol. Before the start of the study, a series of training steps will be implemented to carry out the assessments and training programs. The initial assessment T0 consists of explaining how the study will be conducted, the importance of the research, collecting anthropometric variables (body mass, stature, and body mass index), assessing clinical aspects and the impact that fibromyalgia causes to the patient and other variables such as pain intensity and affect. In addition, familiarization with the exercises and testing of maximum repetition loads will be performed in the following exercises: bench press, front pulldown, leg press, and seated leg curl. The loads found in this evaluation are used in the training protocols (Figure 3).

**FIGURE 3 pri70101-fig-0003:**
[figure not shown]
Proposed exercises.

The T1 assessment will be performed respecting a 7‐day interval after the T0 assessment. At this interval, the patient will return and we will perform the first training protocol drawn on that day (T1). In addition, we will collect the following variables: pain intensity and affect before and after training, total training volume, and subjective effort after training.

The T2 and T3 assessments will follow the same procedure as T1, with a 7‐day interval between each protocol (T1, T2 and T3), so that the patient will perform the other two training protocols. The protocol draw will take place on the respective days of each assessment (T2) and (T3). If the envelope of the protocol drawn has already been performed on previous days, the patient will be instructed to perform a new draw.

Finally, at the T4 assessment, one week after the T3 assessment, the patient will be asked by telephone by the same evaluator (T0 baseline) about his preference for the programs performed in the study (with 1, 2 or 3 sets), standardizing the same commands used in person throughout the study. The following is a description of the three types of training programs with different volumes. The only different training variable will be the number of sets in the three training protocols of the study (Table 1).

**TABLE 1 pri70101-tbl-0001:** Training protocol.

Training (protocol)	Exercise	Sets (*n*)	Repetitions (*n*)	Load (1RM)	Rest (minute)
1	1–4	1	10	60%	2
2		2			
3		3			

*Note:* 1RM: One‐repetition maximum test. Each patient will receive the exercise session individually, as each of the three training protocols has different volumes (i.e., 1, 2, or 3 sets), consequently, the durations will vary for each patient; and then the durations will be compared between the groups.

### Assessments and Data Management

2.7

In order to meet the research objectives, the initial assessments will be detailed to establish the baseline of the study, in addition to the examination data of the predetermined outcomes. Information such as: age, level of education, anthropometric data (stature and body mass), time of diagnosis, weekly physical activity time, patient expectations regarding the proposed training protocols and clinical data of the patient, such as the impact caused by the disease. These data will only be collected during the initial assessment in order to characterize the sample of patients.

### Load Test

2.8

To determine the training loads that will be used in this research, we chose to use a regression equation that predicts the value of the maximum load by performing a submaximal effort in the exercises proposed by the research, for the following reasons: minimizing the risk of injury, for better clinical applicability, and for the high degree of reliability compared to the one‐repetition maximum test in resistance exercises (O'Connor and Simmons 1989).

In addition, the study will evaluate women with fibromyalgia who have low exercise tolerance and high activity withdrawal (Vancampfort et al. 2024). To this end, we selected a submaximal effort test with the best reliability and reproducibility compared to the widely used one‐repetition maximum test, and thus found a prediction equation with the highest correlation and lowest standard error correlated with the one‐repetition maximum test, namely, one repetition maximum = load × [1 + (0.025 × lreps)] (Lacio et al. 2010).

The warm‐up program will be the same as that used in the conventional one‐repetition maximum test, where: each patient will perform a series of 5–10 repetitions, with a load equivalent to 40%–60% of the maximum load perceived before each proposed exercise. After respecting a 2‐min recovery interval after warming up, the subject will perform a series with the highest number of repetitions he/she can in each exercise. At this time, the evaluator will instruct the patient as follows: “Now, perform the highest number of repetitions you can”.

The evaluation of the loads in the exercises proposed in this research will be carried out in the T0 evaluation. The exercises, barbell bench press, front pulldown, 45° leg press, and seated leg curl, will be performed on supertech machines.

### Outcomes

2.9

The primary outcome will be preference. Preference will be assessed by the following question: “After completing the training sessions, which one did you prefer?”. The preference will be assessed at T5. Secondary outcomes will be expectation, pain intensity, affect, and perceived effort, training volume, and cadence. Table 2 summarizes the assessment times and their respective outcomes.

**TABLE 2 pri70101-tbl-0002:** Outcome assessments.

Variables	T0	T1			T2			T3			T4
		A	B	C	A	B	C	A	B	C	
Primary outcome											
Preference											✓
Secondary outcome											
Expectation	✓										
Pain intensity	✓	✓	✓	✓	✓	✓	✓	✓	✓	✓	
Affect		✓	✓	✓	✓	✓	✓	✓	✓	✓	
Perceived effort			✓			✓			✓		
Training volume			✓			✓			✓		
Cadence			✓			✓			✓		

*Note:* A: Pre. B: Post: C: 24h. T0: Initial assessment. T1: Assessment will be performed respecting a 7‐day interval after the T0 assessment. T2 and T3: assessments will follow the same procedure as T1, with a 7‐day interval between each protocol (T1, T2 and T3), so that the patient will perform the other two training protocols (Figures 1, 2, 3). T4: assessment one week after the T3 assessment.

### Expectation

2.10

The Likert scale will be used for treatment expectations. This scale is designed to assess the patient's expectations of the treatment they will receive at the beginning of the study with the following questions (Beasley et al. 2017):Do you think that if you start the workout with 1 set, you will: (1) get a lot worse, (2) get a little worse, (3) neither get better nor worse, (4) get a little better, and (5) get a lot better.You think that if you start the workout with 2 sets, you will: (1) get a lot worse, (2) get a little worse, (3) neither get better nor worse, (4) get a little better, and (5) get a lot better.You think that if you start the workout with 3 sets, you will: (1) get a lot worse, (2) get a little worse, (3) neither get better nor worse, (4) get a little better, and (5) get a lot better.

### Pain Intensity

2.11

The intensity of widespread pain is assessed using the numerical pain rating scale, a self‐report instrument validated for Portuguese (Ferreira‐Valente et al. 2011). The Numeric Pain Scale has a sequence of numbers (from 0 to 10), where 0 represents “no pain” and 10 represents “the worst pain imaginable”. A reduction of 2 points in pain intensity is considered a minimal clinically important difference (Farrar et al. 2001). The numerical pain scale is answered by the patients at three time points: at the beginning, at the end, and 24 h after the end of each resistance training session.

### Affect

2.12

The affective valence scale will monitor pleasure or displeasure during the three resistance training programs and will be conducted using the affective valence scale. The scale is quantified as follows: +5 to −5, corresponding, respectively, to the two antagonistic descriptors of the feeling during physical exercise and/or physical activity, which can be: “very good” and “very bad”. In addition, the affective valence scale presents other intermediate descriptors, which are: +3 = good, +1 = fairly good, 0 = neutral, −1 = fairly bad, and −3 = bad (Hardy and Rejeski 1989). The affective valence scale is completed by the patients at three times: at the beginning, at the end, and 24 h after the end of each resistance training session.

### Subjective Perception of Effort

2.13

The intensity of each resistance training session will be quantified using the subjective perception of effort method. This is done by asking the following question: “How was your exercise session?” The answer will be given, as recommended, 30 min after the end of the session using a scale adapted from Borg (Borg 1982). Patients will be instructed to select a descriptor and then a number from 0 to 10, which may be given in decimals (e.g., 4.5). The scale used will present the following descriptors: 0 = rest; 1 = very, very easy; 2 = easy; 3 = moderate; 4 = somewhat difficult; 5 = difficult; 7 = very difficult; 10 = maximum. The maximum value (10) should be compared to the greatest physical effort experienced by the individual, and the minimum value should be compared to the state of absolute rest (0).

### Training Volume

2.14

Training volume is one of the acute variables of resistance training that is manipulated according to the goal, level of conditioning, and specific recommendations for each individual (Pontes‐Silva, Dibai‐Filho, et al. 2023). Therefore, at the end of each training session, the total training volume of the session will be recorded in a spreadsheet. The training volume was calculated in this study as follows: number of sets × number of repetitions × load (external = kilos lifted per exercise) × subjective perception of effort (values provided by the Borg scale), which provides a value in arbitrary units (Macfarlane et al. 2017; Rausch Osthoff et al. 2018).

### Cadence

2.15

Physical effort in resistance training can also be obtained by measuring the cadence time of each repetition during a given series (concentric phase and eccentric phase), in this case using a mathematical model that replaces the values provided by subjective effort with the effort time performed (Pontes‐Silva 2024a). Thus, in the present study, we will use a stopwatch to measure the effort time of each series, where this stopwatch will be triggered at the beginning of each movement of each series and paused at the end, with this value recorded in a spreadsheet.

### Participant and Audience Engagement

2.16

Patients will not be involved in the design of the study, the formulation of the research question, or the development of recruitment procedures. At the end of the study, the results may be reported to the patients in the form of a presentation of the effects found on the variables studied. If superiority of one program over another is found, this will be reported to the research patients.

### Sample Size

2.17

Sample size calculation was performed a priori using G*Power software (version 3.1.9.7) with the Chi‐squared test for comparisons between the proportions of self‐reported preferences observed in the contingency tables. We calculated the sample seeking an effect size of 0.8 in the difference in the primary outcome (preference). That is, *w* = 0.8, α = 0.05, β = 0.80, degrees of freedom = 25, non‐centrality parameter λ = 23.04, and critical Chi‐squared test = 37.65 (Gignac and Szodorai 2016; Pontes‐Silva 2023). Thus, the sample was estimated to be 36 patients.

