### Statistical Methods

2.18

For the primary outcome (preference), the number of choices of the 3 types of training will be recorded as a percentage. For the analysis of the primary outcome, we will summarize the patient's preference in a contingency table, compare the proportions using the chi‐squared test, and finally verify the effect size of the observed differences. For the secondary outcomes, statistical analyses will be performed by a blind statistician using commercial software. The independent variables of group and time (T0, T1, T2, T3, T4) will be considered for each dependent variable: pain intensity, subjective effort, affect and satisfaction. The Kolmogorov–Smirnov test was used to verify the distribution of the data and the Levene test was used to analyze the homogeneity of variance.

A mixed design analysis of variance will be conducted for the primary and secondary outcomes with a normal distribution, with time as the within‐subject factor and group as the between‐subject factor. If the data are not normally distributed, the Friedman test is used. Time × group interactions and between‐ and within‐group differences were analyzed for all variables. Finally, the Bonferroni test is used in post hoc analyses to determine whether there are differences between‐groups at different intervention times. A 5% significance level and 95% confidence interval will be used for all statistical analyses.

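### The sample size rests on a chi-squared test with 25 degrees of freedom, but a choice among three protocols has 2, so the stated critical value, power and detectable effect do not belong to this trial

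*Protocol article*

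**What the plan says.** Section 2.17 (Sample Size) reports an a priori G*Power calculation "with the Chi‐squared test for comparisons between the proportions of self‐reported preferences observed in the contingency tables". The inputs and outputs printed there are w = 0.8, α = 0.05, β = 0.80, "degrees of freedom = 25", "non‐centrality parameter λ = 23.04" and "critical Chi‐squared test = 37.65". From these, "the sample was estimated to be 36 patients".

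Section 2.18 (Statistical Methods) describes the analysis being sized: "the number of choices of the 3 types of training will be recorded as a percentage", after which the investigators will tabulate the preferences and "compare the proportions using the chi‐squared test".

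Two other sections fix the shape of the data. Under section 2.6 (Intervention and Comparator), each patient is asked once, at T4, which of the programs with 1, 2 or 3 sets she prefers. Under section 2.5 (Randomization), every patient performs all three protocols and acts as her own control.

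**The concern.** The degrees of freedom of a chi-squared test follow from the table being tested. One answer per patient among three options, in a single group, gives a one-way table with three cells and hence 2 degrees of freedom. Twenty-five would need something like a 6 × 6 table or a single question with 26 answers, and the trial has neither.

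The degrees of freedom set the critical value and, through it, the power. Section 2.17 is the article's only statement of what the trial can detect. If it is wrong:

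- A null result will be misread. Readers would take the trial as able to find only an extreme preference, when it can find a considerably smaller one.
- The margin for drop-out is hidden. On the printed calculation, losing one patient takes power below 80%.
- If the printed critical value were carried into the analysis, the primary test would be far too strict.

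The same paragraph gives β as 0.80. β is the type II error, so read literally the trial would have 20% power.

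**Working it through.** **Inputs.** From section 2.17: w = 0.8, α = 0.05, df = 25, λ = 23.04, critical value 37.65, n = 36. From sections 2.6 and 2.18: three response categories, one answer per patient. From section 2.5: no parallel groups.

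**Formulas.** λ = n·w². The critical value c is the upper 5% point of the central chi-squared distribution on df degrees of freedom. Power = P(χ²(df, λ) > c), with χ²(df, λ) non-central.

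**Step 1: reproduce the plan's figure with df = 25.**
- c = 37.652 (printed 37.65).
- λ = 36 × 0.8² = 36 × 0.64 = 23.04 (as printed).
- Power is 0.804 at n = 36 and 0.789 at n = 35, so 36 is the smallest n that reaches 80%.

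The critical value and the sample size both follow from 25, so this is not a misprint. They also show that 0.80 is the power: with β = 0.80 taken literally (power 0.20), df = 25 would give n = 10.

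**Step 2: look for a table with 25 degrees of freedom.**

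| Table | df | Critical value | n for w = 0.8, 80% power | Power at n = 36, w = 0.8 |
|---|---|---|---|---|
| Three choices, one-way | 2 | 5.99 | 16 | 0.994 |
| Draw position × choice (3 × 3) | 4 | 9.49 | 19 | 0.983 |
| Sequence × choice (6 × 3) | 10 | 18.31 | 26 | 0.936 |
| As printed | 25 | 37.65 | 36 | 0.804 |

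The two-way rows are the other tables one could build from this design. Neither gives 25.

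**Step 3: recompute with df = 2.**
- Power at n = 36, w = 0.8 (λ = 23.04): 0.994. Exact multinomial enumeration of the Pearson test gives 0.995.
- Smallest n for w = 0.8: n = 15 (λ = 15 × 0.64 = 9.60) gives 0.798, and n = 16 (λ = 10.24) gives 0.825. So n = 16.
- Effect detectable at n = 36 with 80% power: w = 0.517 (λ = 36 × 0.517² ≈ 9.6). Exact power at this w, with the other two protocols chosen equally often, is 0.806.

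**Step 4: translate w into preference shares.** With a null of 1/3 each, w² = 3·Σ(pᵢ − 1/3)². If the favoured protocol has share 1/3 + d and the other two have 1/3 − d/2 each, then w² = 3(d² + d²/2) = 4.5d², so d = w/√4.5.
- w = 0.8: d = 0.377, giving about 71.0 / 14.5 / 14.5%.
- w = 0.517: d = 0.244, giving about 57.7 / 21.1 / 21.1%.
- A milder 50/30/20 split: w² = 3(0.02778 + 0.00111 + 0.01778) = 0.14, λ = 36 × 0.14 = 5.04. Power is 0.507 by the non-central approximation and 0.537 by exact enumeration.

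**Step 5: what the printed critical value would mean in counts.** With 36 patients, each expected count is 36/3 = 12.
- 30/3/3: χ² = (18² + 9² + 9²)/12 = 40.5, above 37.65.
- 29/4/3: χ² = (17² + 8² + 9²)/12 = 36.2, below 37.65.
- 19/9/8: χ² = (7² + 3² + 4²)/12 = 6.17, above 5.99.

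With the remainder split as evenly as possible, the printed threshold needs 30 of 36 patients to agree, whereas the threshold for three categories needs 19.

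**The case against.** The strongest objection concerns severity. The error is conservative: for its own target of w = 0.8 the trial has more power than claimed, enrolment need not change, and section 2.18 does not commit the analysis to 25 degrees of freedom or to 37.65. All of that stands. It means that no patient enters a trial underpowered for the stated effect, and that misuse of the printed threshold is a risk rather than a plan. It does not make the paragraph correct, and the fault is a wrong statement, which a full protocol or analysis plan elsewhere would not excuse.

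A second objection is that the article speaks of contingency tables and never names a one-way test or a null of one third each. That also stands as to wording. One question with three answers in a single group makes the one-way reading the natural one, and the two-way tables that the design allows have 4 or 10 degrees of freedom, so neither rescues 25.

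Third, the article gives no preference shares, and w does not determine them. About 66/33/1 also corresponds to w ≈ 0.8, and about 45.5/45.5/9 to w ≈ 0.52. The splits quoted here are illustrations under equal shares for the other two protocols.

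Fourth, the exact size of the Pearson test with cut-off 5.99 at n = 36 is 0.060 rather than 0.05, so part of the small gain in exact over approximate power comes from that excess. The effect on the conclusions is negligible.

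**Conclusion.** The point holds: the calculation is wrong as written. The arithmetic in section 2.17 is consistent with itself, but the degrees of freedom entered do not match the primary outcome. With 2 degrees of freedom the critical value is 5.99 instead of 37.65, power at w = 0.8 and n = 36 is 99.4% instead of 80%, and the effect detectable with 80% power is w ≈ 0.52 instead of 0.8. The printed β is the power.

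This rests on reading the primary test as a one-way comparison of three shares against equal preference; the translation into shares further assumes that the two less popular protocols are chosen equally often. The sample size is adequate for the stated target. It is not adequate for every preference that might matter: a 50/30/20 split has only about 54% power.

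**What to change.** Keep 36 patients and rewrite the paragraph in section 2.17 to state:

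- the test: one-way chi-squared goodness of fit, three categories, null of 1/3 each, df = 2, critical value 5.99, α = 0.05;
- the power as 1 − β = 0.80, in place of β = 0.80;
- what n = 36 delivers: 80% power at w ≈ 0.52 (for example about 58/21/21) and 99% power at w = 0.8;
- the drop-out margin: at w = 0.8, power stays at or above 80% down to 16 completers.

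If the investigators intend a two-way table instead, they should name its rows and columns and give the matching degrees of freedom. Because w ≈ 0.52 is what the fixed sample size can detect, and not a target chosen in advance, it should be labelled as such. Section 2.18 should name the same test. The cost is one reworded paragraph and a clause in section 2.18, with no change in enrolment or conduct.

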### Statistical Methods

2.18

For the primary outcome (preference), the number of choices of the 3 types of training will be recorded as a percentage. For the analysis of the primary outcome, we will summarize the patient's preference in a contingency table, compare the proportions using the chi‐squared test, and finally verify the effect size of the observed differences. For the secondary outcomes, statistical analyses will be performed by a blind statistician using commercial software. The independent variables of group and time (T0, T1, T2, T3, T4) will be considered for each dependent variable: pain intensity, subjective effort, affect and satisfaction. The Kolmogorov–Smirnov test was used to verify the distribution of the data and the Levene test was used to analyze the homogeneity of variance.

A mixed design analysis of variance will be conducted for the primary and secondary outcomes with a normal distribution, with time as the within‐subject factor and group as the between‐subject factor. If the data are not normally distributed, the Friedman test is used. Time × group interactions and between‐ and within‐group differences were analyzed for all variables. Finally, the Bonferroni test is used in post hoc analyses to determine whether there are differences between‐groups at different intervention times. A 5% significance level and 95% confidence interval will be used for all statistical analyses.

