### Randomization, Allocation, Blinding, Patient Timeline, and Data Collection Methods

2.5

Randomization will be performed before each training protocol, taking into account the 3 different types of training protocols. The order in which the patient will perform the training protocol will be determined by a simple draw in an envelope containing 3 papers described as 1 series, 2 series, or 3 series. Therefore, if in the first session the patient draws the paper described as 1 series, in the following week this paper will be removed from the envelope and the same will draw 2 or 3 series, and so on.

In this way, all patients involved in the study will randomly perform the 3 types of protocols proposed in the study, and they will be their own controls. To avoid allocation bias, opaque sealed envelopes will be used, with sequential numbers on the outside of the envelope. This allocation will be made by Researcher B, who will not be involved in any other study procedures. Patients selected in the screening conducted by Researcher A who agree to participate in the research will be randomly assigned.

Regarding blinding, all assessments will be performed by Researcher A, who will not be involved in the interventions and will not participate in the delivery of the training protocol. Each patient will remain identified by numbers and not by name. In order not to compromise the blinding of the study, all patients will undergo the same assessment before and after the training session. Due to the nature of the proposed intervention (physical exercise), the therapist and patients will not be blinded to the intervention. Patients will be instructed not to disclose any information to other patients and/or researchers.

At the end of the T3 training protocol, with a 7‐day interval between these assessments, we will conduct T4, where each patient will be asked which training protocol they prefer. After T4, researcher D will tabulate the data, which will be delivered to researcher E, who will be responsible for the statistical analysis and who will not participate in the previous phases of the research (Figure 2).

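### The primary outcome is given two conflicting analyses: an ANOVA/Friedman that cannot apply to one nominal choice per patient, and a contingency-table chi-squared test that does not describe three counts with 2 degrees of freedom

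*Protocol article*

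**What the plan says.** All references are to the protocol article.

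- **Outcomes (2.9).** Preference is the primary outcome, measured by one question: "After completing the training sessions, which one did you prefer". Table 2 ticks it only at T4. Intervention and Comparator (2.6) describes the answer as a choice between the programmes with 1, 2 or 3 sets.
- **Randomization (2.5).** The design is a crossover in which "all patients involved in the study will randomly perform the 3 types of protocols proposed in the study, and they will be their own controls".
- **Statistical Methods (2.18), first paragraph.** For preference, "the number of choices of the 3 types of training will be recorded as a percentage". The analysis is to summarise "preference in a contingency table, compare the proportions using the" chi-squared test, followed by an effect size.
- **Statistical Methods (2.18), second paragraph.** "A mixed design analysis of variance will be conducted for the primary and secondary outcomes with a normal distribution". Its factors are time, taken within patients, and group, taken between patients. A fallback is given for non-normal data: "If the data are not normally distributed, the Friedman test is used".
- **Sample Size (2.17).** The calculation is for a chi-squared test for "comparisons between the proportions of self"-reported preferences in contingency tables, with w = 0.8, α = 0.05, 25 degrees of freedom, λ = 23.04 and critical value 37.65, giving 36 patients.

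**The concern.** The same section sends the only primary endpoint to two different analyses. One of them, the ANOVA or its Friedman fallback, presupposes a response measured repeatedly and, for the ANOVA, separate groups of patients. Preference has neither.

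The other is described in terms that do not fit the data. A contingency-table test examines the association between two classifications of independent units. Here there is one classification, the programme chosen, and one record per patient. No second classification is named, and the 25 degrees of freedom in Sample Size cannot come from three categories.

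The wording matters because an analyst who takes the contingency table literally has to build a two-way table from one-way data. The obvious way to do so repeats patients, which makes the test anticonservative.

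**Working it through.** **Inputs.** N = 36, w = 0.8, α = 0.05, df = 25, λ = 23.04 and critical value 37.65 (Sample Size); three categories, one choice per patient (2.6, 2.9, Table 2). The null of equal thirds and the 3 × 2 layout below are assumptions; the protocol states neither.

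**1. The plan's own figure.** λ = N × w² = 36 × 0.64 = 23.04. The 95% point of chi-squared with 25 df is 37.65. Power from the noncentral chi-squared is 78.9% at N = 35 and 80.4% at N = 36. The stated 36 therefore reproduces, but only with df = 25.

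**2. Degrees of freedom the data support.** Three counts summing to 36 have 3 − 1 = 2 df. A df of 25 would need, for example, 26 categories in a one-way table (26 − 1) or a 6 × 6 two-way table (5 × 5). Nothing in the protocol yields either. With df = 2 and w = 0.8, 80% power needs 16 patients. At N = 36 power is 99.4%, and the effect detectable with 80% power is w = 0.52.

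**3. Can the ANOVA or Friedman test be applied to preference?**

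| Requirement | What the protocol provides |
|---|---|
| Numeric response, normally distributed (ANOVA) | A nominal choice of 1, 2 or 3 sets |
| Repeated measurement over time (ANOVA) | One question, at T4 only |
| Between-subject group (ANOVA) | None; every patient does all three protocols |
| A score or rank for each condition from each patient (Friedman) | One choice, with no score or ranking of the three |

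No requirement is met.

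**4. What a literal contingency table could do.** Assume rows are the three protocols and columns are chosen / not chosen. Each patient supplies one chosen and two not-chosen entries: 3 × 36 = 108 dependent entries. Under equal thirds the expected counts are 12 and 24. With nᵢ the number choosing protocol i:

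- Goodness-of-fit: G = Σ(nᵢ − 12)²/12, df = 2.
- 3 × 2 table: T = Σ(nᵢ − 12)² × (1/12 + 1/24) = 1.5 × G, also referred to df = 2.

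The 5% critical value is 5.991, so the 3 × 2 table rejects when G exceeds 5.991/1.5 = 3.994. Asymptotically this has probability exp(−3.994/2) = 13.6%. Exact enumeration of the multinomial with N = 36 and equal thirds gives:

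| Test at nominal 5% | Actual type I error |
|---|---|
| Goodness-of-fit, asymptotic critical value | 6.0% |
| Goodness-of-fit, exact p-value (chi-squared ordering) | 4.0% |
| 3 × 2 protocol by chosen/not chosen | 14.0% |

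**5. Example.** For a split of 18/9/9, Σ(nᵢ − 12)² = 36 + 9 + 9 = 54. Then G = 54/12 = 4.5 (p = 0.105) and T = 6.75 (p = 0.034). The same 36 answers fall on opposite sides of 5%.

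**The case against.** **The chi-squared sentence can be read as the right test.** It speaks of the number of choices of three types of training, of proportions compared by chi-squared, and of an effect size. That is a fair description of a one-sample goodness-of-fit test, and an article may leave the null proportions and layout to a fuller document. This stands in part: it would be too strong to say that neither stated analysis fits. But the repeated contingency-table wording and the df of 25 do not describe that test, so the text does not commit to it.

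**The 14.0% is not a property of the plan.** This stands. A reader might infer that the trial will run at nearly three times the nominal error. The documents define no rows or columns, and df = 25 fits a 3 × 2 table no better than it fits goodness-of-fit. Against the 6.0% actual size of asymptotic goodness-of-fit, the ratio is 14.0/6.0 = 2.3 rather than 2.8. Under the planned w = 0.8, with one protocol favoured and the other two equal, the two layouts disagree in only about 0.35% of trials (power 99.5% against 99.8%); the concern lies at or near the null.

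**Recording as a percentage.** A reader might also infer that percentages will be entered into the test as if they were counts. The sentence describes how choices are recorded, and nothing says percentages will be the test input.

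**The ANOVA phrase may be a drafting slip.** The abstract gives only chi-squared for preference, and the list of dependent variables for the group-and-time analysis omits it. The ANOVA is also limited to normally distributed outcomes. All of this is true, but the Friedman fallback catches whatever is not normal, so the text still assigns preference to an inapplicable test. Because that test cannot be run, it offers little real opportunity to choose a method after seeing the data, and the 18/9/9 example does not measure any harm from this conflict.

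**Conclusion.** The point holds in limited form. Two parts rest on the text alone. First, Statistical Methods assigns the primary outcome to both a chi-squared test and an ANOVA/Friedman analysis, and the latter cannot apply to a single nominal answer in a trial without between-subject groups. Second, the contingency-table wording and df = 25 do not match three counts with df = 2.

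The error rate is conditional. If the table were laid out as protocol by chosen/not chosen, type I error at N = 36 would be 14.0%, against 6.0% for asymptotic goodness-of-fit and 5% nominal. If the analyst runs goodness-of-fit, that inflation does not arise. The sample is not too small for the df = 2 test: 36 patients exceed the 16 needed at w = 0.8.

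**What to change.** 1. Name one primary analysis in Statistical Methods: a one-sample chi-squared goodness-of-fit test on first-choice counts, or its exact multinomial version, with one record per patient, null proportions of 1/3 each and df = 2. Report Cohen's w and confidence intervals for the three proportions.
2. Remove the primary outcome from the ANOVA sentence, so that it and the Friedman fallback cover secondary outcomes only.
3. Restate Sample Size with df = 2. The figure of 36 can stay, described as giving 99.4% power at w = 0.8, or 80% power at w = 0.52.

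The cost is two sentences in Statistical Methods and a matching correction in Sample Size. Visits, recruitment and data collection are unaffected. If the exact version with chi-squared ordering is chosen, it is slightly conservative (actual size 4.0%).
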